### Sample size

An annual IS recurrence rate of 4% is assumed in the monotherapy group, based on data from patients receiving aspirin monotherapy in the Japanese Aggrenox Stroke prevention versus Aspirin Programme (JASAP) study and Effective Vascular Event REduction after STroke (EVEREST) 9,29. According to Lakatos and Lan's method 30, at least 1688 patients per group would be required for the primary analysis using the log-rank test to detect a 30% relative risk reduction in the DAPT group with 80% power, a two-sided type I error of 0·05, a recruitment period of 2·5 years, and a maximum follow-up period of 3·5 years. Assuming an annual discontinuation rate of 5%, the target number of randomized patients is therefore 2000 per group, or 4000 in total. The 4000 patients will be enrolled in Japan between October 2013 and March 2016.

### Statistical analysis

Efficacy and safety analyses will be performed on the basis of the intention-to-treat (ITT) population. The treatment groups will be compared using the log-rank test. Cox proportional hazard models will be used to calculate the hazard ratio and its 95% confidence intervals for the DAPT group, compared with the monotherapy group. The hazard ratio will be adjusted for age, sex, type of IS (atherothrombotic or lacunar), and modified Rankin Scale (mRS). Annual recurrence rates will be estimated using the person-year method and the Kaplan–Meier method, and their 95% confidence intervals will be calculated using the approximate Poisson and Greenwood methods. Subgroup analyses will be performed following stratification by age, sex, antiplatelet agents (aspirin, clopidogrel), type of IS (atherothrombotic or lacunar stroke), stenosis of extracranial arteries, mRS, medical history and complications (hypertension, diabetes mellitus, dyslipidemia, coronary heart disease, peripheral arterial disease, chronic kidney disease, IS), smoking status, obesity, and microbleeds. Tests for interaction between the treatment arm and subgroup will be performed using the Cox proportional hazards model. Interim assessment of the safety and efficacy end-points will be conducted when the cumulative person-year exposure has reached 50% of the target. Early termination of the trial will be decided primarily on the basis of the Haybittle-Peto ad hoc method 31,32. Although no termination criteria are specified with regard to the safety end-points, the independent data monitoring committee (IDMC) may recommend early termination based on the incidence of adverse events within the DAPT group.

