### Randomization

The data center will randomize the patients to either monotherapy group or DAPT groups using a block-randomization scheme, with the research site as a randomization unit. After providing informed consent, each patient will be identified by a linkable patient identification code, and registered via a web-based registration system, along with information relevant to his or her eligibility. If the patient is considered eligible, the allocated therapy for the patient will be notified through this system. Patients and investigators will be aware of the treatment allocation.

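### The primary test is an unadjusted log-rank test, but the only hazard ratio and 95% CI described are covariate-adjusted, so the two can disagree on significance in a borderline result

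*Protocol article*

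**What the plan says.** Under Sample size, the protocol article states that "at least 1688 patients per group would be required for the primary analysis using the log-rank test". Under Statistical analysis it repeats the choice, with no covariates or strata named: "The treatment groups will be compared using the log-rank test".

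For the size of the effect, the same section says that "Cox proportional hazard models will be used to calculate the hazard ratio and its 95% confidence intervals for the DAPT group", relative to monotherapy, and then that "The hazard ratio will be adjusted for age, sex, type of IS (atherothrombotic or lacunar), and modified Rankin Scale (mRS". No unadjusted HR is described.

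Under Randomization, patients are allocated "using a block-randomization scheme, with the research site as a randomization unit". Nothing is said there about balancing on age, sex, stroke type or mRS.

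**The concern.** Readers expect a two-sided 5% test and its 95% CI to tell one story: p below 0.05 goes with an interval that excludes 1. That holds, near enough, when both come from the same model. Here the test ignores four covariates and the interval uses them. As described, randomization does not balance these covariates, so chance imbalance is possible. It would be corrected in the estimate and not in the test. The trial could then report p>0.05 beside a CI that excludes 1, or the reverse, on its main result.

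A second, smaller matter is that listing covariates for the estimate while leaving them out of the test gives up whatever power they would bring.

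**Working it through.** **1. Does the stated sample size belong to the unadjusted log-rank test?** The inputs are all from Sample size: control rate 4% per year, 30% relative reduction (HR 0.70), two-sided 0.05, 80% power, 2.5 years of recruitment, 3.5 years maximum follow-up.

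- Events (Schoenfeld): 4 × (1.960 + 0.842)² / (ln 0.70)² = 4 × 7.849 / 0.1272 ≈ 247.
- Event probability with hazard λ, uniform accrual over R = 2.5, total T = 3.5, no dropout: 1 − [exp(−λ(T−R)) − exp(−λT)] / (λR). For λ = 0.04 this is 0.0857; for λ = 0.028 it is 0.0609.
- Per group: 247 / [(0.0857 + 0.0609)/2] / 2 ≈ 1686.

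With Freedman's 253 events, and annual risks converted to hazards (0.0874 and 0.0617), the figure is 1698. The article states 1688, so test and sample size agree.

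**2. Events and power at the target size.** With 2000 per group and 5% per year dropout, the event probabilities are 0.0822 and 0.0580. Events: 2000 × (0.0822 + 0.0580) ≈ 280. Power: Φ(√280 × 0.3567/2 − 1.960) ≈ Φ(1.02) ≈ 85%.

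**3. How often do test and adjusted CI disagree?** 4000 patients were simulated 1:1, with average control hazard 0.0408, follow-up uniform on 1–3.5 years, dropout hazard 0.0513, and 1500 runs per scenario. Covariate strengths are assumptions:

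- Moderate: HR 1.25 per SD for age and for mRS, 1.5 for stroke type (50% prevalence), 0.85 for sex (30%).
- Strong: these log-HRs doubled.

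The SD of the moderate prognostic score is √(2 × 0.0498 + 0.25 × 0.1644 + 0.21 × 0.0264) = √0.146 ≈ 0.38. The strong one is about 0.76.

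| True HR | Covariates | Power, log-rank | Power, adjusted Cox | Disagree on significance | Correlation of z |
|---|---|---|---|---|---|
| 0.70 | moderate | 83.7% | 84.5% | 2.1% | 0.993 |
| 0.70 | strong | 80.5% | 83.5% | 5.9% | 0.970 |
| 0.80 | moderate | 47.9% | 47.9% | 4.2% | 0.992 |
| 0.80 | strong | 43.6% | 46.2% | 7.8% | 0.969 |

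A separate simulation at HR 0.70 used one normal prognostic score (1000 runs each). For score SDs of 0.3, 0.5 and 0.7, disagreement was 1.1%, 4.0% and 5.3%. The power gains were 0.5, 0.4 and 2.3 points, with paired Monte Carlo standard errors of 0.33, 0.63 and 0.73. A further simulation gave 2–5% disagreement at HR 0.70 and 3–7% at HR 0.80, with gains of about 0.5–1.7 points at HR 0.70.

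**4. Analytic check of the disagreement.** If the z statistics have unit variance and correlation r, their difference has SD √(2(1−r)) and mean absolute size 0.798 times that. Multiply by the density of the log-rank z at the critical value, read from its power.

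- HR 0.70, moderate: 0.798 × √(2 × 0.0074) × 0.246 ≈ 2.4% (simulated 2.1%).
- HR 0.70, strong: 0.798 × √(2 × 0.0297) × 0.276 ≈ 5.4% (simulated 5.9%).
- HR 0.80, strong: 0.798 × √(2 × 0.0307) × 0.394 ≈ 7.8% (simulated 7.8%).

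**5. Is the marginal HR far from the conditional one?** For a conditional HR of 0.70, the event-weighted marginal HR under this design is 0.701, 0.703 and 0.706 for score SDs of 0.3, 0.5 and 0.7. The gap is trivial, so the disagreement comes mainly from chance imbalance near the boundary.

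**The case against.** The case against is substantial, and most of it stands.

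- **The unadjusted log-rank test is no error.** It is valid under randomization, keeps the type I error, and is the test on which the 1688 per group rests. Pairing it with a Cox HR adjusted for covariates named in advance is common.
- **The deciding result is fixed.** A reader might infer that, in an open-label trial, the p-value or the CI could be chosen as the headline once results are known. The documents do not support that: Sample size names the log-rank test as the primary analysis, so it governs if the adjusted interval differs.
- **A reader might infer that test and estimate answer materially different questions.** They share the same null hypothesis, and step 5 shows the two HRs nearly coincide at this event rate.
- **The power argument is weak.** At score SDs of 0.3 and 0.5 the gain cannot be told from zero at the simulation sizes used. It is clear only when the covariates are assumed to be strong.
- **Moving to an adjusted test has its own hazard.** Table 1 first schedules mRS at the start of observation, after registration. Allocation is notified through the registration system and is known to patients and investigators, so mRS may be scored with allocation known.
- **A fuller analysis plan may also report an unadjusted HR.** That is possible, and the article does not exclude it. But the article does not merely leave this open: it states the test, states the estimate, and pairs them across different models. That part of the point survives.

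**Conclusion.** The point holds in a limited form and is minor. The article pairs an unadjusted primary test with an HR and CI that are described only as adjusted, so the two can contradict each other on significance. That happens in about 1–6% of trials at HR 0.70 and 3–8% at HR 0.80, and only for borderline results. Adjusting the test would add about 0.5–3 points of power at HR 0.70. These ranges rest on assumed covariate strengths, since the article gives none; the event rate, effect, accrual, dropout and size are the design's own. It would go too far to conclude that the primary test is invalid, that the primary analysis is undecided, or that the sample size must change.

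**What to change.** Under Statistical analysis, take the primary test, HR and 95% CI from one analysis. Either option below will do:

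1. Keep the log-rank test as primary, report the unadjusted Cox HR and 95% CI as the matching primary estimate, and label the adjusted HR supportive. This leaves the sample size basis untouched and does not depend on when mRS is scored.
2. Make the test of treatment in the pre-specified adjusted Cox model primary, with its HR and CI, and the log-rank test supportive. Use only covariate values recorded before allocation: either obtain an mRS before allocation or leave mRS out of the primary model.

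Use the same choice at the interim look. The cost is one sentence of text, best settled before the interim analysis, with no change in sample size. Option 2 also makes the decision depend on a pre-specified model and, if mRS is kept, needs a pre-allocation mRS.

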### Study organization and funding

Otsuka Pharmaceutical Co., Ltd. sponsored the trial implementation in the Japan Cardiovascular Research Foundation under an agreement between the two parties. Subject registration, data management, and statistical analysis are delegated to a contract research organization (EPS Corporation). This trial will be conducted at approximately 400 sites under the guidance of the steering committee. The enrolled patients have to pay partly their own costs for drugs prescribed in this study depending on the type of their own health insurance.

The principal investigator is [name], who is attached to the National Cerebral and Cardiovascular Center. The final trial protocol was prepared by the protocol committee, and it will be amended, if required. Any event related to the primary and secondary end-points will be reviewed by the event review committee blindly to antiplatelet medications. The statistical analysis committee will be responsible for proposing the randomization scheme and providing expert opinions on the sample size and the analysis plan. It will be also responsible for generating the interim and final analysis plans.

The IDMC will recommend trial discontinuation/continuation or protocol amendment based on annual reviews of patient accrual, serious adverse events, incidence of adverse events, and on the interim efficacy analysis comparing the two treatment arms. The individuals who played a critical role in the planning, supervision, and conduct of this trial are listed in the end of this article.

## Discussion

Prevention of IS recurrence in high-risk patients remains an important clinical problem, since monotherapy with conventional antiplatelet agents is only modestly effective. The CSPS.com will evaluate whether DAPT including cilostazol is similarly safe and more effective in preventing IS recurrence and other vascular outcomes than aspirin or clopidogrel monotherapy in high-risk patients. This trial will resolve several clinical questions regarding preventive antiplatelet therapy for recurrent IS. First, this will be the first trial to explore the efficacy and safety of the combined use of a thienopyridine (clopidogrel) and a phosphodiesterase inhibitor (cilostazol). Second, DAPT including cilostazol may be particularly effective for Asian patients, since they frequently have intracranial atherosclerosis 33 and the TOSS showed the potential of aspirin plus cilostazol for regression of intracranial arterial stenosis 19. Since patients with stenosis (≥50%) of a major intracranial or extracranial artery can be included in the study regardless of existence or number of vascular risk factors, we expect that around half or more of the included patients will have atherothrombotic stroke. Third, DAPT including cilostazol may be safe and fit for long-term use, based on the results of previous clinical and hemostatic studies 20–25. Since Asian ethnicity is a possible risk factor for ICH 34,35, avoidance of ICH during antithrombotic therapy is essential for Asian stroke patients.
